\* We will examine the potential for a *multiplier effect of the advocacy training*. In the pilot, GC-CCP increased CC advocacy among intervention recipients, as well as the alters who were targeted with advocacy. Diffusion of advocacy may heighten uptake of CC screening throughout networks and larger community via increased CC knowledge, peer support, and stigma reduction. Unlike the pilot, the proposed study will assess the prevalence, quality and effects of advocacy conducted by 1st degree alters of the index participants, and the social network members of these alters (2nd degree alters), as well as explore how these intervention effects may attenuate the further the advocate is from direct exposure to the GC-CCP advocacy training.

\* Most hybrid designs rely on the study team to train and supervise intervention personnel, despite the need to study implementation processes in a real-world context. We will start with the study team training facilitators to implement GC-CCP, but then *transfer training and supervision duties to clinic staff who will be trained and mentored* to take on this role for the majority of the study. This will enable us to identify barriers and facilitators to implementation and sustainability of GC-CCP across diverse (urban/rural, public/private) clinic settings.

If shown to be an effective implementation strategy for promoting health screening and other health behaviors, this peer advocacy model could be applied to other disease contexts in both LMIC and high resource settings.

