**D2.2.1 Multi-site RCT of CC-CCP.** At all 4 sites, 40 women screened for CC in the past year will enroll as index participants (n=160), with 20 randomly assigned to the intervention, and 20 to a wait-list usual care control. Individual randomization entails contamination risks, but statistical models suggest  $\geq 30\%$  of the control arm must receive the equivalent of a full-strength intervention for meaningful contamination. We decided against an attention control, because attention paid to intervention (index) participants would not impact alter behavior (primary outcome), and its policy implications would be less clear. The intervention arm will be divided into 2 groups of 10 (balanced on ages 25-35 and 36+) for receipt of the intervention. The control arm receives the intervention after the 12-month follow-ups. Each index participant will recruit up to 3 alters (total= ~440 alters; referred to as 1st degree alters) with no history of CC screening. All index and 1st degree alter participants will be followed up at months 6 and 12. At month 6, 1st degree alters will recruit up to 2 of their own alters (2nd degree alters; total= ~800) who they report targeting with advocacy and thereafter getting screened for CC; 2nd degree alters will be administered a single, brief phone interview.

**Eligibility criteria:** *Index participants:* female, age 25+ (the lower limit for recommended CC screening), screened for CC in past year (clinic records), and no advanced stage disease (12-month follow-up is feasible). *1st degree alters:* female, age 25+, and report no CC screening history. *2nd degree alters:* female and age 25+.

**Recruitment** of index and 1st degree alters will span 8 weeks (5 index and 14 alters per week) at each site. Clinic staff will contact eligible women who have been screened for CC in the past year to inform them of the study; if interested, the site coordinator will perform consent processes and formal eligibility screening. Eligible women who enroll will complete the baseline survey, followed by randomization as an index participant.

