**1st degree alters:** The site coordinator will use the social network assessment within the baseline survey of each index to randomly select (using a random number table) 5 alters who know the participant's CC screening experience (or as many as there are if < 5) and ask the index if she is comfortable recruiting 3 of these alters. The index will be asked to call each selected alter at the end of their baseline interview to describe the study in the presence of the coordinator (or later in private, if she prefers), who will schedule a study visit for the alter. If an alter refuses or cannot be reached, a replacement will be randomly chosen from the original list of 5 alters.

**2nd degree alters:** The site coordinator will use the social network assessment in the month 6 survey of each 1st degree alter to randomly select 4 alters (or as many as there are if < 4) who the alter reports targeting with CC screening advocacy and thereafter was screened for CC. A similar process as described above for 1st degree alters, will be used to recruit and enroll 2nd degree alters. The coordinator will obtain verbal consent from the 2nd degree alter over the phone and the complete a brief 15-minute phone survey.

**Assessment schedule:** Surveys will be administered at baseline, month 6 and month 12 for index and 1st degree alters, and 2nd degree alters will be surveyed only once (at month 6 assessment of 1st degree alters). Participants will receive 30,000 Ush (~\$8) per assessment, except 2nd degree alters who will receive 10,000 Ush (via mobile money). To limit attrition, we will collect tracking information (phone numbers and mapped addresses), including contacts for family/friends with whom they have frequent contact. Clinic staff will help us track clients we have difficulty reaching. In the pilot, >96% of index and alters were retained at month 6.

**Measures:** Survey assessments for index and 1st degree alter participants will be interviewer-administered in Luganda using Network Canvas software, last ~ 75 minutes, and include a social network assessment. CC screening and treatment utilization will be verified with medical chart data.

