**Social network assessment:** The participant will list 10 female alters (which is adequate for structural and compositional variability) with whom they interact most. For each listed alter, we will gather information to assess *network composition* (e.g., age, relation to respondent, history of CC screening and treatment; knowledge of respondent's CC screening experience). In the index survey only, we will ask how if each alter knows each other alter to assess *network structure* (e.g., density); this section is time consuming, so given the large number of alter participants, alters will not complete this survey component. Research questions related to this section [e.g., do denser networks promote more CC screening within the network) will be addressed with index participant data. To assess CC advocacy and perceived effects, from the perspective of both the index and alter, we will ask the participants if they have engaged in CC screening advocacy (separate items for discussed, encouraged, gave info, gave direct support, and frequency) with the specific alter in the past 6 months, and any perceived resulting action (e.g., alter was screened). At follow-up, we will determine whether listed alters are the same or unique from those listed at baseline, to facilitate longitudinal analyses of alter data.

**Phone assessment of 2nd degree alters** will assess background characteristics, receipt of CC screening and treatment services, CC knowledge, receipt of CC screening advocacy from referring 1st degree alter, engagement in CC prevention advocacy (general), number of alters engaged in CC screening advocacy with, and the number of these alters perceived to have been screened for CC following this advocacy.

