Harm from CC risk disclosure or advocacy. Among the goals of the intervention sessions are to improve the participants' ability to make effective decisions regarding disclosure of their CC risk status and engaging in CC prevention discussions with members of their social network. These sessions will be designed to help participants recognize the full range of responses that they may encounter when disclosing their status or discussing CC, including the potential for recipients of such information to act with hostility, discrimination, or other negative responses. Hence, the sessions focus on decision making regarding these behaviors, and improving judgment for when such behaviors will be beneficial versus harmful, rather than encouraging all participants to disclose or advocate prevention regardless of risk for harm. These procedures cannot prevent all negative responses, but should minimize such risks. In the pilot of the intervention, no adverse events were reported in this regard.

**Inadvertent CC risk disclosure to recruited social network member:** Index participants will be asked to consider recruiting up to 3 of their network members to participate in the study survey, and 1st degree alters will be asked to recruit up to 2 of their social network members. Participants will be informed that this is not a requirement and that they should only ask people who they are comfortable with approaching to participate. These participants will be asked to consider selecting these network members from a list of 5 randomly selected network members (generated by the study) whom they report know the participant's CC screening experience/result (if there are less than 5 named members who know the participant's CC screening experience/result, then only those who do know will be selected). This procedure should limit the risk of the participant trying to recruit a network member who does not know the participant's CC screening experience/result, but participants are allowed to recruit network members who are not on the list of 5 members provided to them by the study, so it is possible. However, participants will be counseled on the risks of approaching such a network member, as someone who does not know the index participant's CC screening experience could assume the index participant has CC or CC risk given the nature of the study.

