## **F. DATA SAFETY AND MONITORING PLAN**

### **I. Description of Study and Study Data**

This study is a partnership among RAND Corporation ([name] and [name], MPIs), Makerere School of Public Health ([name], MPI), African Palliative Care Association, Rays of Hope Hospice Jinja, and Indiana University at Bloomington. We will conduct a hybrid implementation-effectiveness randomized controlled trial (RCT) of *Game Changers for Cervical Cancer Prevention (GC-CCP)*, a 7-session peer-led group intervention that aims to empower and mobilize women who have screened for cervical cancer (CC) to be agents for CC screening and prevention in their social networks. For the RCT, we will recruit 160 screened women (index participants) across 4 clinics, randomizing 80 to the intervention and 80 to the usual care control condition. Each index participant will be asked to recruit up to 3 social network members (1st degree alters) who have never screened for CC to complete assessments (~440 total based on average of 2.75 alters recruited per index participant, 220/arm) over 12 months, to test intervention effects on alter uptake of CC screening. All participants will complete surveys at baseline, and 6- and 12-months post-baseline. At the

month 6 follow-up, first degree alters will be asked to recruit up to 2 of their social network members (2nd degree alters; ~ 800 total). Surveys of index and alter participants will include questions about CC screening, CC knowledge, CC stigma, and engagement in CC prevention advocacy. Data on alter CC screening and treatment will be extracted from medical records. All data will be collected and stored at the participating clinic sites initially, and then transferred to Makerere University School of Public Health; de-identified data will be transferred to RAND for data management and analysis.

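### Second-degree alters are sampled only after reported advocacy and screening, so their phone survey cannot support the arm and attenuation comparisons of Aim 3, and the target of about 800 sits at the ceiling

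*Protocol*

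**What the plan says.** **Sampling rule.** Section D2.2.1 states the restriction twice. The design summary has first-degree alters recruit women "who they report targeting with advocacy and thereafter getting screened for CC". The recruitment paragraph for second-degree alters tells the site coordinator "to randomly select 4 alters (or as many as there are if < 4") from those "who the alter reports targeting with CC screening advocacy and thereafter was screened for CC". Each first-degree alter may recruit two, and each recruit has one short phone interview.

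**Eligibility.** The criteria in the same section ask only that second-degree alters be "female and age 25" or older. They contain no advocacy or screening condition.

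**A third description.** Section E.4 (Protection Against Risk) says that first-degree "degree alters will be asked to recruit up to 2 of their social network members". It then describes a list of five randomly selected members who know the participant's screening experience, and allows recruits from outside that list.

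**Purpose.** Aim 3(b) in section A asks for mediators and moderators of intervention effects on the advocacy of index participants and of first- and second-degree alters. Section C (Innovation) adds the intention to "explore how these intervention effects may attenuate the further the advocate is from direct exposure to the GC-CCP advocacy training".

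**Measurement.** Under Measures in D2.2.1, the phone survey records screening and "receipt of CC screening advocacy from referring 1"st degree alter. It also records knowledge, the woman's own advocacy, how many women she advocated with, and how many of those she believes were then screened.

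**Target.** About 800 second-degree alters, from first-degree alters numbering "440 total based on average of 2.75 alters recruited per index participant, 220/arm" (section F.I).

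**The concern.** A second-degree woman enters the sample only if a first-degree alter advocated to her and she was then screened. If the intervention works, it changes both how often this happens and to whom. The interviewed women in the two arms are then not comparable groups, although the index participants were randomized.

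At stake are the about 800 interviews meant to inform the multiplier question, out of 1,400 planned RCT participants (section E.1). The second-degree woman's own advocacy, which is the Aim 3(b) outcome at that level, is collected nowhere else. Because she is interviewed once, there is no baseline measure to adjust for. The rule also limits how many women can qualify, most of all in the control arm.

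**Working it through.** **1. What the rule does to each item**

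| Phone-survey item | Effect of the rule |
|---|---|
| Own screening | Near 100% in both arms, apart from misreporting (in the pilot, an index participant who believed an enrolled alter had been screened was right 88% of the time; section D.1) |
| Advocacy received from the first-degree alter | Near 100% in both arms, apart from misreporting |
| Knowledge, own advocacy, women advocated to and then screened | Free to vary, but compared between groups selected on consequences of treatment |

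Attenuation has a further problem. First-degree alters are enrolled unscreened at baseline. Second-degree alters are enrolled at month 6 as completed advocacy successes. Distance from the training is therefore confounded with selection on response to advocacy.

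**2. Reproducing the target**

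The protocol gives no derivation of 800. Inputs: 440 first-degree alters (section F.I); at most 2 recruits each (D2.2.1); 10% planned attrition and 96% month-6 retention in the pilot (Statistical Analysis, Power).

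- 440 × 0.90 × 2 = 792
- 440 × 0.96 × 2 = 845
- 440 × 1.00 × 2 = 880

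The first matches the stated figure closely. Mean recruits needed per retained alter:

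- 90% retention: 800 / 396 = 2.02, above the cap of 2
- 96% retention: 800 / 422.4 = 1.89

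At 96%, if every intervention alter supplies two (211.2 × 2 = 422.4), control alters must average (800 − 422.4) / 211.2 = 1.79. Under the model in step 3, about 28% of each control alter's named network would have to be targeted and then screened.

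**3. Expected yield under the stated rule**

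The documents give no rate for first-degree alters' own networks, so this step rests on assumptions. Each alter names 10 women (Social network assessment, D2.2.1). The pilot shares of index participants' named networks perceived as screened at month 6, 57% intervention and 14% control (section D.1), are taken to apply to first-degree alters' networks. Every screened woman counts as advocated to, all accept, and networks do not overlap.

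With X ~ Binomial(10, p), expected recruits per alter are E[min(X, 2)] = 2 − 2·P(X=0) − P(X=1).

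- Intervention, p = 0.57: 2 − 2(0.0002) − 0.0029 = 2.00
- Control, p = 0.14: 2 − 2(0.221) − 0.360 = 1.20

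| Retention | Alters per arm | Intervention | Control | Total | Ratio |
|---|---|---|---|---|---|
| 90% | 198 | 395 | 237 | 632 | 1.7:1 |
| 96% | 211 | 422 | 253 | 675 | 1.7:1 |

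**4. Less favourable assumptions**

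- Same rates, with between-alter heterogeneity (beta-binomial correlation 0.3) and 80% acceptance: 488 (350 + 138) at 90% retention; 520 (373 + 147) at 96%.
- Advocacy weakening at the second step (assumed 30% and 5%): 488 (385 + 103) at 96% retention with no heterogeneity and full acceptance, down to 303 (249 + 54) at 90% with both penalties.

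**The case against.** The strongest reply is that the study does not depend on the phone survey alone. At month 6 every retained first-degree alter, in both arms, lists 10 women and reports advocacy with each and any perceived result. These reports are not selected on screening. They allow a comparison by randomized arm of how many women were advocated to and perceived as screened. This stands. A reader might infer from the sampling rule that the trial cannot show diffusion at all; the documents do not support that. The phone survey can also describe completed chains. What the network reports cannot supply is the second-degree woman's own advocacy or knowledge.

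A reader might also infer that a planned second-degree screening contrast is forced to zero. No such contrast is specified: Aim 3(b) concerns advocacy, and the attenuation statement is worded as exploration. The near-constant screening item is a limit of the survey, not a failed endpoint.

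On numbers, one might suppose that only first-degree alters who were themselves screened can supply recruits, which gives totals of 166 to 317. Nothing in the protocol says so, and it ignores the 10-name list. Nor must every retained alter supply two: at 96% retention the mean needed is 1.89. The target is worded as approximate and carries no power calculation.

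Finally, if the eligibility line governed instead of the recruitment paragraph, the selection problem would disappear and about 800 would be a feasible near-ceiling figure. But the restrictive rule is the operational instruction and appears twice, so sites following the text would apply it.

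**Conclusion.** The point holds for the phone survey. As written, the rule selects on two consequences of the intervention. An arm comparison of second-degree women's own advocacy is then biased in a direction the documents do not settle, and the attenuation comparison cannot be interpreted.

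The target of about 800 is at or near the maximum the design allows: 792 at 10% attrition, 845 at 96% retention. Under generous use of pilot network rates the rule yields about 632 to 675, with roughly 1.7 intervention women per control woman; the less favourable scenarios shown give about 300 to 520. These yields depend on assumed rates for first-degree alters' networks and are a range, not a forecast. The shortfall falls mainly in the control arm.

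Severity is moderate and confined to Aim 3. The primary outcome and its power rest on first-degree alters and are unaffected.

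**What to change.** **Preferred.** Before month-6 visits begin, draw second-degree women aged 25 or over at random from each first-degree alter's 10-name list, without conditioning on advocacy or screening. Keep two recruits plus replacements. Alternatively, oversample advocated women with known probability and weight back. Analyse by randomized arm with clustering by index participant.

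**Safeguards and text.** Keep the voluntary approach and disclosure counselling of section E.4. Reconcile the two sampling statements in D2.2.1, the list described in E.4 and the eligibility line. Settle whether the E.4 list applies to second-degree recruitment: first-degree alters are unscreened at baseline, so choosing women who know their screening experience would again select on a post-randomization event.

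**Cost.** The number of calls is the same. Fewer interviewed women will have received advocacy, so detail on its quality will be thinner. A broader draw may also reach women who know less about the recruiter, which makes the counselling more important.

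**If only successful chains are wanted.** Label the sample descriptive, drop arm-effect and attenuation claims from it, rest second-degree arm comparisons on the first-degree network reports (perceived, not verified), and restate the target as a realistic range.

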| Survey Constructs                                                                                                                   | Instrument                                                                       |
|-------------------------------------------------------------------------------------------------------------------------------------|----------------------------------------------------------------------------------|
| Primary Outcome                                                                                                              |                                                                                  |
| CC screening (VIA) and results                                                                                                      | Survey; medical chart                                                            |
| Secondary Outcomes                                                                                                           |                                                                                  |
| CC-related treatment (e.g., cryotherapy, thermal therapy; radiation); biopsy                                                        | Survey; medical chart                                                            |
| CC prevention and treatment advocacy (general)                                                                                      | 6 items; dev. In- house; alpha=.95                                               |
| CC screening advocacy with specific alter (discussed/encouraged/gave info/direct support)                                           | 4 items; dev. In-house; alpha=.87                                                |
| CC screening advocacy received from index as perceived by alter (discussed/encouraged/gave info/direct support) (alter survey only) | 4 items; dev. In-house; alpha=.86                                                |
| Potential Mediators                                                                                                          |                                                                                  |
| CC knowledge (etiology, prevention, treatment)                                                                                      | 16 items; dev. in-house; alpha=.75                                               |

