| Reach (CC screened women and their alters)                                            | b) Proportion and characteristics of research enrolled women who receive GC-CCP (i.e., index participants) who engage in advocacy
c) Proportion and characteristics of research enrolled alters who received advocacy from index participant
d) Proportion and characteristics of research enrolled alters who engage in advocacy with other alters                                                              | Survey data collected during RCT; intervention vs control comparison (Implementation)                                                                                                                                              |
| Effectiveness (alters)                                                                | Proportion of previously unscreened alters who get screened for CC,                                                                                                                                                                                                                                                                                                                                                    | Med chart (intervention vs control group in RCT; Implementation)                                                                                                                                                                   |
| Adoption (Clinic staff)                                                               | Clinic staff integrate GC-CCP (i.e., extent to which staff identify, train, and supervise peer facilitators, recruit clients, conduct sessions):

 
Proportion of staff who report recruiting clients for GC-CCP
 
Extent to which staff supervisor carries out weekly supervision of peer facilitators conducting GC-CCP sessions
 
                            | Twice yearly survey of clinic staff implementation activities (Sustainment)
Clinic staff supervisor fidelity forms (Sustainment)                                                                                                |

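### A 1st degree alter can list the index woman who recruited her, so a conversation led by the index can be scored as the alter's own advocacy, more often in the intervention arm

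*Protocol*

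**What the plan says.** **How the list is built.** Protocol D2.2.1, Social network assessment: "The participant will list 10 female alters", chosen as those the respondent interacts with most. This applies to index and 1st degree alter surveys alike; alters skip only the questions on ties between listed women. For each name, and explicitly from both the index's and the alter's perspective, respondents are asked about the past 6 months: "if they have engaged in CC screening advocacy (separate items for discussed, encouraged, gave info, gave direct support, and frequency) with the specific alter".

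**Outcomes that use these items.** The Survey Constructs table lists as a secondary outcome "CC screening advocacy with specific alter (discussed/encouraged/gave info/direct support)", a 4-item scale. Next to it stands a separate 4-item scale with the same verbs, "CC screening advocacy received from index as perceived by alter (discussed/encouraged/gave info/direct support) (alter survey only)". A 6-item general advocacy scale is also a secondary outcome and does not use the list.

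**Reach (d).** Table 2 in D.2.3 defines it as "Proportion and characteristics of research enrolled alters who engage in advocacy with other alters", taken from RCT survey data and compared between arms.

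**How alters are chosen.** Under D2.2.1 recruitment, 1st degree alters are drawn from the index's own list, among women who already know of her screening experience.

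**The concern.** Each 1st degree alter is among the women her index interacts with most, so the index is a plausible name on the alter's own list. No rule in the recruitment, survey-construct, network-assessment or data-description text removes her.

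Three of the four items (*encouraged*, *gave info*, *gave direct support*) make the respondent the giver. *Discussed* does not. An alter who only listened to her index can truthfully say that they discussed screening. The same conversation can then score twice: as advocacy received from the index, and as advocacy by the alter.

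The intervention trains index women to start such conversations, and controls are not trained until after month 12, so the misclassification would differ by arm. What is at stake is evidence on onward diffusion: an arm difference in list-based alter advocacy could appear without any additional alter having approached another woman.

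**Working it through.** The Protocol states no figure for this quantity, so there is nothing to reproduce. The check is a comparison of texts, then an illustration.

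**Texts side by side**

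- The D.2.2 specification table describes the diffusion step as alters who received advocacy going on to advocate with other alters, and gives the action target as unscreened alters. Table 2, Reach (d), also refers to other alters.
- The recruiting index fits neither description: the eligibility criteria require her to have been screened in the past year.
- The list rule in D2.2.1 still admits her. The construct points away from her and the measurement does not.

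**Illustration: score is any listed advocacy (yes/no), with no true diffusion**

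Inputs, all assumed because the Protocol gives none:

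- b: share of alters with own advocacy to someone other than the index, 0.20 in both arms.
- q: share of alters who list the index, 0.10 to 0.50.
- Share of listing alters with whom the index discussed screening: 0.90 intervention (pI), 0.50 control (pC).

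Arm rate = b + (1 − b) × q × p. False difference = (1 − b) × q × (pI − pC).

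| q | Intervention | Control | False difference |
|---|---|---|---|
| 0.10 | 0.2 + 0.8×0.1×0.9 = 27.2% | 0.2 + 0.8×0.1×0.5 = 24.0% | 3.2 points |
| 0.30 | 0.2 + 0.8×0.3×0.9 = 41.6% | 0.2 + 0.8×0.3×0.5 = 32.0% | 9.6 points |
| 0.50 | 0.2 + 0.8×0.5×0.9 = 56.0% | 0.2 + 0.8×0.5×0.5 = 40.0% | 16.0 points |

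A weaker contrast (0.70 versus 0.50, q = 0.30, b = 0.40) gives 0.6 × 0.3 × 0.2 = 3.6 points.

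**Chance that the false difference reaches p < 0.05.** The Power paragraph gives 220 alters per arm, 10% attrition and an upper ICC of 0.05; the Data Safety and Monitoring Plan gives 2.75 alters per index. Effective size = 198 / (1 + 1.75 × 0.05) = 182 per arm. At that size the chance is about 10%, 48% and 87% for the three rows, and about 10% for the weaker contrast.

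**Alternative score: mean over 10 names and 4 items, scaled 0 to 1.** One *discussed* answer for one name is 1/40 of the score, so the shift is q × (pI − pC) / 40. At q = 0.50 this is 0.5 × 0.4 / 40 = 0.005.

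**With the recruiting index left out,** the false difference by this route is 0 under either score.

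**The case against.** **Scoring and item wording belong in documents not shown.** How a secondary score is derived is ordinary SAP content, and the parenthesised verbs are labels, not questionnaire text. This stands as a limit on certainty: it cannot be said that the conversation will be miscounted. It does not remove the point, because the Protocol itself fixes who may be listed and which items are asked. If the survey never records who started the conversation and the index is not identified on the list, later analysis cannot recover it.

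**Direction is already stated.** The items sit under a stem about engaging in advocacy, the Types of Data section speaks of advocacy provided (with the index as respondent), and advocacy received has its own scale. This makes misreporting less likely on three items. It does not take a *yes* on *discussed* off the given scale.

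**Reach (d) already says other alters.** True, and that favours leaving the index out; but no rule carries it out.

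**The multiplier claim has other support.** A reader might infer that the whole of Aim 3(b) and the multiplier claim could be an artefact. The Protocol does not support that. Aim 3(b) speaks of prevention advocacy, which matches the general 6-item scale, and no text ties it to the list. Recipients also report: 2nd degree alters say whether they received advocacy from the referring alter. They must have been screened after that advocacy, so an index screened before entry would qualify only if screened again.

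**The assumed inputs could be too generous.** An alter on the index's list need not list the index in return. Control alters also know the index's screening experience and are also called by her about the study, so their *discussed* rate may be high. This is why the illustration uses 50% for controls and starts at 10% of lists.

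**Conclusion.** The point holds in limited form. The list-based alter advocacy outcome, and Reach (d) if scored from the list as any advocacy, can show an intervention effect produced by the index's own conversations. The path is clear only for *discussed*, and only when the index is listed.

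Under the stated assumptions the false difference runs from about 3 to 16 points for a yes/no score and is negligible for a 10-name mean. A reader might choose stronger inputs, for example the index on 50% to 90% of lists and discussion rates of 80% versus 20%. The arithmetic then gives 0.8 × 0.5 × 0.6 = 24 to 0.8 × 0.9 × 0.6 = 43 points. The Protocol supplies none of those values and no any-yes rule, so such figures should not be presented as the expected bias.

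The primary outcome, alter screening, is untouched, and the general 6-item scale does not run through the list. The change is still worth making before alter surveys are fielded, because it costs almost nothing and matches the Protocol's own definition of onward advocacy.

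**What to change.** In both arms and at all waves:

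1. Flag the recruiting index wherever she appears on a 1st degree alter's list. First name and last initial are already collected for listed women (Types of Data). The file linking study numbers to participant names stays with MakSPH, so set the flag at interview or before data transfer.
2. Leave her out of the alter's list-based advocacy score and out of Reach (d), and state this rule in D2.2.1 and Table 2.
3. Word *discussed*, as advocacy given, as a conversation the respondent started.

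Do not drop every listed woman who was already screened. The D.2.2 specification table treats continuing advocacy for periodic screening as legitimate, and women first named at follow-up have no baseline record to filter on. At most, report that restriction as a sensitivity analysis.

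Cost: one flag, one scoring rule and one change of item wording. Slightly fewer listed women count per alter, and the reported alter advocacy rate may be lower.
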